## Abstract

**Background:**

Periodontitis causes progressive attachment loss, which in turn causes tooth mobility and, ultimately, tooth loss. Regenerating and rebuilding the lost periodontal tissue is the goal of periodontal regenerative surgery. Regeneration using AmnioGuard, advanced platelet-rich fibrin (A-PRF), and NovaBone Putty has been demonstrated to be successful in increasing clinical attachment level and decreasing probing pocket depth.

**Objective:**

This study aims to compare and evaluate the effectiveness of AmnioGuard and A-PRF membrane in combination with NovaBone Putty in the regeneration of human periodontal infrabony defects.

**Methods:**

A total of 24 patients will be selected and divided into 2 groups: group A (n=12, 50%) and group B (n=12, 50%). Group A will receive treatment with NovaBone Putty and AmnioGuard, whereas group B will receive treatment with autologous A-PRF and NovaBone Putty. Plaque index, clinical attachment level, probing pocket depth, complete mouth bleeding score, and intraoral periapical radiographs will be statistically analyzed. Clinical and radiographic features will be evaluated before surgery and 6 months following the procedure.

**Results:**

Recruitment began on September 16, 2025, and is ongoing. As of manuscript submission, 4 participants have been enrolled. Results are expected to be published in 2027. All the clinical measurements will be recorded after 6 months. It can be anticipated that AmnioGuard membrane with NovaBone Putty will provide additional benefits in the management of chronic periodontitis by promoting better healing and clinical outcomes.

**Conclusions:**

Within the constraints of this study, the AmnioGuard membrane combined with NovaBone Putty may be more effective in the treatment of chronic periodontitis.

## Introduction

### Background

A dysbiotic dental biofilm that gradually destroys bone and periodontal attachment is a hallmark of periodontitis, a chronic, multifactorial, inflammatory illness. This condition negatively affects speech, mastication, aesthetics, psychological well-being, and overall quality of life [1]. On the basis of bone resorption patterns, periodontal defects are traditionally classified as supraosseous (suprabony) or infraosseous (infrabony). Goldman and Cohen [2] further categorized infrabony defects by the number and configuration of residual osseous walls surrounding the periodontal pocket. Infrabony defects pose a significant clinical challenge as they require both structural regeneration and the restoration of periodontal function. Regeneration is defined as “the reproduction or reconstitution of a lost or injured part to restore the architecture and function of the periodontium” [3]. To achieve this, regenerative periodontal therapy aims to stimulate the formation of new bone, periodontal ligament, and cementum. NovaBone Putty, a next-generation calcium phosphosilicate material derived from bioactive glass, offers multiple advantages for regeneration. It is osteoconductive, osteostimulative, and biocompatible, with hemostatic and anti-inflammatory effects. Its premixed formulation enhances clinical handling and allows for optimal defect adaptation [4]. AmnioGuard, a human amniotic membrane (AM)–based barrier, has also gained attention due to its anti-inflammatory, antifibrotic, antibacterial, and antiscarring properties. Its high laminin subunit alpha-5 content supports epithelial adhesion and accelerates healing, whereas its role as a biological barrier aids in preventing epithelial downgrowth—an essential aspect of guided tissue regeneration (GTR) [5-7]. In recent years, biological membranes have become increasingly important in regenerative therapies. Since their initial application in skin grafting in 1910, their role has expanded across medical and dental fields. In particular, AmnioGuard has shown potential to reduce microbial penetration and modulate wound healing responses [8]. In addition, advanced platelet-rich fibrin (A-PRF), rich in leukocytes, contributes to regeneration by releasing growth factors such as transforming growth factor beta 1, epidermal growth factor, and insulin-like growth factor, all of which enhance fibroblast proliferation and tissue healing [9]. Although several studies have assessed the individual regenerative potential of NovaBone Putty and AmnioGuard, limited clinical data directly compare their effectiveness in managing periodontal infrabony defects. A study conducted by Hazari et al [10] compared NovaBone Putty and platelet-rich fibrin (PRF) and concluded that, in comparison to NovaBone Putty alone, PRF in conjunction with NovaBone Putty produced more favorable findings in terms of relative attachment level gain and higher reduction in probing pocket depth (PPD). A study by Kothiwale et al [11] in which they assessed and compared the effectiveness of bovine-derived xenogenic bone graft (Bio-Oss) and demineralized freeze-dried bone allograft using AM as GTR determined that, while there was no discernible difference between the two materials, both showed a notable improvement in bone fill and percentage gain. Furthermore, evidence regarding clinical outcomes such as probing depth reduction, attachment level gain, and bone fill remains sparse [12]. Therefore, this study aims to address this gap by directly comparing the clinical and radiographic outcomes of NovaBone Putty in combination with A-PRF or AmnioGuard in the treatment of infrabony periodontal defects.

### Objectives

This study aims to evaluate and compare the effectiveness of AmnioGuard and A-PRF in combination with NovaBone Putty in terms of gain in clinical attachment level (CAL), reduction in PPD, and radiographic bone fill in infrabony defects before surgery and 6 months after surgery.

## Methods

### Ethical Considerations

The Institutional Ethics Committee of Datta Meghe Institute of Higher Education and Research, Sawangi (Meghe), Wardha, Maharashtra, India, approved this study (reference DMIHER(DU)/IEC/2025/507). Participants will be provided with an informed consent form clearly describing the study’s aim, procedures, risks, and benefits and their right to opt out at any time. Consent for publication of data will be obtained and used for all analyses, including secondary analyses. We will confirm that the original consent and institutional review board approval explicitly cover the use of primary and secondary data. Collection of data and entering of the data into the database for screening and randomization will be conducted by the primary investigator. The privacy of prospective and enrolled participants’ personal information will be upheld to ensure confidentiality before, during, and after the trial. We will ensure that the data collected are fully anonymized, with no personally identifiable information retained or linked to any participant. As there are no interventions involved and only a cross-sectional survey will be conducted in which the data will be collected via an interview and anthropometric measurements, participants will not be provided with any compensation in this study. For any images presented in the manuscript, appropriate consent will be obtained from the participants.

### Recruitment

#### Overview

Participants in this clinical trial will be those receiving treatment at the Department of Periodontics and Implantology of Sharad Pawar Dental College, Datta Meghe Institute of Higher Education and Research, or those referred for treatment there who have periodontal pockets larger than or equal to 4 mm in at least 10 permanent teeth. All clinical procedures will be performed there. It is thought that this will enhance trial adherence and recruitment because patients will already be receiving treatment at this location.

#### Inclusion Criteria

The inclusion criteria are as follows: (1) at least 1 or 2 interproximal infrabony osseous defects that may be seen on radiography, with a PPD of at least 5 mm and clinical attachment loss of at least 5 mm after starting treatment; (2) clinical and radiographic measurements showing that the intraosseous component of the lesion is ≥3 mm deep (intraoperative assessment will confirm this); (3) defect radiographic base of at least 3 mm coronal to the tooth’s apex; and (4) keratinized gingiva surrounding the test teeth of at least 3 mm wide to completely hide the deficiency with soft tissue.

#### Exclusion Criteria

The exclusion criteria are as follows: (1) patients with evident localized aggressive periodontitis, (2) individuals with poor oral hygiene (plaque index >1), (3) those who have recently smoked more than 10 cigarettes per day or who have used tobacco products, (4) a tooth that has not had enough endodontic or restorative care, (5) a tooth that has a class III or class IV furcation defect and mobility greater than grade II, (6) a history of periodontal surgical treatment in the specific quadrant of the mouth selected for the study, and (7) women who are pregnant or nursing mothers.

### Sample Size Estimations

The following calculations were performed to estimate sample size:

Mean PPD for AmnioGuard and NovaBone Putty (μ₁) before: 8.6 (SD 1.17) mmMean PPD for AmnioGuard and NovaBone Putty (μ₂) after: 6.9 (SD 1.10) mmThe standard normal deviate (*Z* value) corresponding to a 2-sided significance level (α) of .05, which equals a 95% confidence level, is given by (1–α/2)=1.96Z_(1–β [β=.05; power=95%]) = 1.64 (Z_(1 − β) represents the standard normal deviate corresponding to the study power. With β set at 0.05 (power=95%), the Z value used was 1.64. This differs from Z_(1 − α/2), which corresponds to the significance level (α = 0.05) used in the sample size calculation).Combining the 2 aforementioned equations yields the following: n≥[(Z_[1 – α/2] + Z_[1 – β])^2^ × (σ₁^2^ + σ₂^2^/r)]/(μ₁ – μ₂)^2^Replacing the aforementioned values into the equation yields the following: n≥[(1.96 + 1.64)^2^ × (1.17^2^ + 1.10^2^/1)]/(8.6 – 6.9)^2^=12

Hence, group 1 and group 2 require a minimum sample size of 12. The minimum total sample size required is 24 [13].

All data will be tested for normality using the Shapiro-Wilk test and for homogeneity of variance using the Levene test to ensure that the assumptions for parametric tests are met.

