### Statistical Analysis

A calculation of means and SDs will be conducted, and the mean data will be analyzed using a standard statistical method to determine statistical significance. Unpaired and paired 2-tailed *t* tests will be used to evaluate data at baseline and 6 months for each group. A *P* value greater than .05 will be considered not statistically significant, whereas a *P* value of less than .05 will be deemed significant. The results will be calculated using the SPSS software (version 17; IBM Corp). Group A and group B will be compared based on clinical outcomes of plaque index, full-mouth bleeding score, PPD reduction, and CAL gain using an unpaired *t* test.

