### Evaluation Outcomes

The primary outcome of this study is radiographic bone fill at 6 months after surgery. This outcome is crucial as it indicates the extent of bone regeneration achieved through the different treatment modalities being tested. The secondary outcomes are PPD reduction, plaque index, papillary bleeding index, and CAL gain.

PPD reduction, which is used to evaluate the decrease in the depth of periodontal pockets, a sign of improved periodontal health, will be measured using an acrylic stent and a UNC-15 probe. Once the acrylic stent is in place, the UNC-15 probe will be positioned at the appropriate angle to access the deepest part of the interproximal pocket within the crevicular space. The point at which the probe makes contact with the stent will be marked in pencil. This will provide a consistent point of reference for subsequent measurements.

Plaque index will be calculated using the Turesky-Gilmore-Glickman modification of the Quigley-Hein index.

Papillary bleeding index will be calculated using the Muhlemann-Son Sulcus Bleeding Index.

CAL gain, which measures the improvement in the attachment of the periodontal tissue to the tooth, indicating successful regeneration, will be measured using a UNC-15 probe positioned at the base of the pocket.

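### The 95% power and the minimum of 24 rest on a within-treatment change in pocket depth, a secondary outcome, so neither applies to the primary bone-fill comparison

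*Protocol article*

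**What the plan says.** All sections cited are in the protocol article.

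- **Sample Size Estimations** uses a Z value "corresponding to a 2-sided significance level (α) of .05". On power it says: "With β set at 0.05 (power=95%), the Z value used was 1.64". It adds that this deviate "represents the standard normal deviate corresponding to the study power", without naming an outcome.
- The only outcome data in that section are two PPD means with SDs, 8.6 mm (1.17) and 6.9 mm (1.10). Both are labelled as AmnioGuard plus NovaBone Putty, one before and one after treatment.
- The section concludes: "Hence, group 1 and group 2 require a minimum sample size of 12", and then "The minimum total sample size required is 24".
- **Evaluation Outcomes** says: "The primary outcome of this study is radiographic bone fill at 6 months after surgery". It continues: "The secondary outcomes are PPD reduction, plaque index, papillary bleeding index, and CAL gain".
- **Statistical Analysis** says that the two groups will be compared on "clinical outcomes of plaque index, full-mouth bleeding score, PPD reduction, and CAL gain using an unpaired" *t* test. Bone fill is not in that list.

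The article gives no bone-fill mean, SD, target difference or power, and no reason for sizing the trial on PPD.

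**The concern.** A power figure belongs to one comparison: a given outcome, a given difference and a given SD. Here the figure is presented as a property of the study, while the outcome behind it is secondary. A reader who puts the sample-size and outcomes sections together will naturally attach 95% to the bone-fill comparison, and nothing in the article supports that.

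There is a second break in the same calculation. The trial compares two arms, but the difference entered is the change over time in one of them. Replacing it with a between-arm PPD difference would still leave the trial sized on a secondary outcome. Replacing PPD with a before-to-after change in bone fill would still not address the between-arm question. The section has to deal with both.

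At stake is how the primary result can be read. The Results section says that no substantial difference between groups is expected. If that proves right, a non-significant bone-fill result is likely, and a printed power of 95% would make it look far more informative than 12 patients per arm allow.

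**Working it through.** **1. Reproducing the plan's figure.** Inputs from Sample Size Estimations: Z values 1.96 and 1.64, SDs 1.17 and 1.10 mm, means 8.6 and 6.9 mm, allocation ratio 1.

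n = (1.96 + 1.64)² × (1.17² + 1.10²) / (8.6 − 6.9)²
= 12.96 × (1.3689 + 1.2100) / 2.89
= 12.96 × 2.5789 / 2.89
= 11.56, rounded up to 12 per group, 24 in total.

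The arithmetic is right. The 95% is an input (it fixes 1.64); only 12 and 24 are computed. The pooled SD is √(2.5789 / 2) = 1.136 mm, so the design difference is 1.7 / 1.136 = 1.50 SD. For a true difference of that size, 12 per arm gives 95.6% power by the normal approximation and 93.9% by the non-central *t* distribution.

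**2. What the 95% refers to.** Both means come from the same treatment at two times. The formula is for two independent groups. The 1.7 mm is therefore not a difference between AmnioGuard and A-PRF, and no A-PRF value enters. If the stated SDs are assumed to hold for the six-month between-arm PPD comparison, non-central *t* power at 12 per arm is:

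| Between-arm PPD difference | Power |
|---|---|
| 0.5 mm | 18% |
| 0.8 mm | 38% |
| 1.0 mm | 54% |
| 1.7 mm | 94% |

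Only the last row comes near 95%, and the article gives no ground for expecting the arms to differ by as much as one arm changes over time.

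**3. What 12 per arm gives for bone fill.** The article has no bone-fill SD, so results are in SD units. Assumptions: two-sided .05, unpaired *t* test with 22 degrees of freedom, one value per patient, no losses.

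| Power | Detectable difference |
|---|---|
| 80% | 1.20 SD |
| 90% | 1.39 SD |
| 95% | 1.54 SD |

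| True difference | Power |
|---|---|
| 0.5 SD | 22% |
| 0.8 SD | 47% |
| 1.0 SD | 65% |
| 1.2 SD | 80% |

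Expected half-width of the 95% confidence interval: t(0.975, 22) × √(2/12) = 2.074 × 0.408 = 0.85 SD.

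No required sample size for bone fill can be derived, because the article gives neither a target difference nor an SD.

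**The case against.** The strongest reply has four parts.

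*The article never attributes 95% to bone fill.* The words about study power define a symbol, and both means are openly labelled as PPD. That is fair, and a reader might go too far by saying that the article claims 95% power for its primary outcome. It does not. But it calls the figure the power of the study, gives no other, and names a different outcome as primary, so the mismatch stands.

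*PPD may be a reasonable basis for sizing.* The article does not argue this, and a PPD change in millimetres says nothing about the variability of bone fill. Nor would it be enough to relabel the calculation as PPD planning. A reader might infer that the 95% is at least valid for PPD, but step 2 shows that it is not the power of the between-arm PPD comparison.

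*The SD-unit figures are generic.* They hold for any unpaired 12-versus-12 *t* test. They also assume one value per patient and no losses, whereas the inclusion criteria allow one or two defects, and the analysis section does not name bone fill for the unpaired test. All of this stands. The figures show what the design can resolve under stated conditions; they do not show that the trial is too small for bone fill, or that 24 is enough. Either conclusion would need a bone-fill SD and target difference that the article does not give.

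*The harm is speculative.* No section says that a non-significant result will be read as similarity. The analysis section only calls it not statistically significant, and the conclusions lean towards AmnioGuard. So the misreading is a risk created by the printed power, not something the authors propose.

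**Conclusion.** The point holds. Neither the 95% nor the 24 derived with it applies to the primary comparison, and the 95% does not describe the between-arm PPD comparison either. The article prints both the full calculation and the outcome hierarchy, so this is a conflict within the stated plan and not a detail left to an unseen analysis plan.

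Under the assumptions in step 3, the bone-fill comparison reaches the printed 95% only if the arms differ by about 1.54 SD. A difference of 0.8 SD would be missed slightly more often than found (47% power). The trial can proceed, but its power statement should not stand as written.

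**What to change.** In Sample Size Estimations:

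- Withdraw 95% as the study power.
- State that the calculation used a within-treatment PPD change and does not give the power of any between-arm comparison.
- Keep 24 as the planned size, without calling it a minimum derived for the primary outcome.
- State what 12 per arm gives for the between-group bone-fill comparison, with its conditions (two-sided .05, unpaired *t* test, one value per patient, no losses, SD units because no bone-fill SD is available): 1.20 SD detectable at 80% power, 1.54 SD at 95%, expected 95% confidence interval half-width about 0.85 SD.

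In Statistical Analysis, add that the between-group bone-fill difference will be reported with its 95% confidence interval, and that a non-significant result will not be interpreted as similarity.

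The cost is a few sentences, and recruitment does not change. The downside is that the stated power becomes less favourable. The article reports 4 participants enrolled at submission and analysis not yet completed, so the text can be corrected before results are known.

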## Results

Ethical approval was obtained from the Institutional Ethics Committee of Datta Meghe Institute of Higher Education & Research on February 7, 2025. Recruitment began on September 16, 2025, and is ongoing. As of manuscript submission, 4 participants have been enrolled. Data collection is ongoing, and data analysis has not yet been completed. Results are expected to be published in 2027.

All the clinical measurements will be recorded at baseline and 6 months. Plaque index, which indicates the degree of full-mouth supragingival plaque accumulation, will be used to assess the patient’s dental hygiene status and will be measured at the 1-month follow-up. Although a substantial difference between the groups is not anticipated, AmnioGuard and NovaBone Putty should show better results and improvement in clinical outcomes such as CAL gain and PPD reduction.

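### The sample size treats the AmnioGuard arm's own before-after PPD change as the between-arm difference, so the stated 95% power does not apply to the comparison the trial makes

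*Protocol article*

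**What the plan says.** Sample Size Estimations sets the error rate as "corresponding to a 2-sided significance level (α) of .05" and the power by "With β set at 0.05 (power=95%), the Z value used was 1.64". The first mean is introduced as "Mean PPD for AmnioGuard and NovaBone Putty (μ₁) before: 8.6 (SD 1.17" and the second, 6.9 mm (SD 1.10), is labelled as the same treatment afterwards. The two values enter a formula for two independent means with allocation ratio r = 1. The conclusion is "Hence, group 1 and group 2 require a minimum sample size of 12", and then "The minimum total sample size required is 24".

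The comparison the trial makes is set out elsewhere in the article:

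- **Objectives and Randomization:** AmnioGuard is compared with A-PRF, each combined with NovaBone Putty, in two randomised groups of 12.
- **Statistical Analysis:** groups A and B are compared by unpaired t test on clinical outcomes that include PPD reduction. Paired tests within each group are also planned.
- **Evaluation Outcomes:** the primary outcome is radiographic bone fill at 6 months. PPD reduction is secondary.
- **Abstract, Background:** regeneration with AmnioGuard, A-PRF and NovaBone Putty "has been demonstrated to be successful in increasing clinical attachment level and decreasing probing pocket depth".

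**The concern.** A two-group sample size needs the expected difference between the groups. The figure used here is how much one group is expected to improve from its own baseline. The two coincide only if the other arm does not improve at all, and the article describes A-PRF as an effective treatment.

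The stated 95% power therefore belongs to a different question from the one the trial asks. It also belongs to a different outcome from the primary one. The sample size rests on this paragraph alone. A reader of the results would take a trial described as having 95% power to be well able to separate the arms, when the interval around the between-arm difference may be close to 1 mm wide on each side.

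**Working it through.** **Inputs from Sample Size Estimations.** Two-sided α = 0.05 (Z = 1.96); power 95% (Z = 1.64); means 8.6 and 6.9 mm; SDs 1.17 and 1.10 mm; r = 1.

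**Step 1: reproduce the stated figure.**

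n = (1.96 + 1.64)² × (1.17² + 1.10²) / (8.6 − 6.9)² = 12.96 × 2.5789 / 2.89 = 11.56, rounded up to 12.

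The arithmetic holds. With a t test in place of the normal approximation, power at 12 per arm for 1.7 mm is 93.9%, and 95% would need 13 per arm. That gap is too small to matter.

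**Step 2: identify the contrast.** Both means carry the same treatment label, one before and one after. The 1.7 mm is thus a within-arm change. No A-PRF mean or SD appears.

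**Step 3: try the paired reading.** A paired calculation would use the SD of the change, √(1.17² + 1.10² − 2ρ × 1.17 × 1.10), where ρ is the before-after correlation. At an assumed ρ = 0.5 it needs 5.8, so about 6 patients. The printed formula equals the paired one only if ρ = 0. Even then it would size a within-arm test, not the comparison of arms.

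**Step 4: what 12 per arm gives for the between-arm comparison.** Statistical Analysis compares PPD reduction, so the relevant SD is that of the change. The documents do not give ρ, so values of 0.3, 0.5 and 0.7 are assumed, with the document's two SDs in both arms:

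- ρ = 0.3: √(2.5789 − 0.3 × 2.574) = √1.8067 = 1.34 mm
- ρ = 0.5: √(2.5789 − 0.5 × 2.574) = √1.2919 = 1.14 mm
- ρ = 0.7: √(2.5789 − 0.7 × 2.574) = √0.7771 = 0.88 mm

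The documents do not give the between-arm difference either, so 0.5 and 1.0 mm are illustrations. Power is from the noncentral t distribution with 22 degrees of freedom. The detectable difference at 80% power is 1.197 × SD. The 95% CI half-width is 2.074 × SD × √(2/12).

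| Assumed ρ | SD of change (mm) | Power, 0.5 mm | Power, 1.0 mm | Detectable at 80% (mm) | CI half-width (mm) |
|---|---|---|---|---|---|
| 0.3 | 1.34 | 14% | 41% | 1.61 | 1.14 |
| 0.5 | 1.14 | 18% | 54% | 1.36 | 0.96 |
| 0.7 | 0.88 | 26% | 76% | 1.06 | 0.75 |

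**Step 5: the primary outcome.** No mean, SD or difference for bone fill is given, so its power cannot be computed from the article.

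**The case against.** Several points on the other side have weight.

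- **The arithmetic is sound.** This stands. The fault lies in what the inputs represent, not in the calculation.
- **The source of the means is not at hand.** The formula has two groups and an allocation ratio, so figures from two arms may have been mislabelled as before and after. That cannot be ruled out, and it is why checking the source comes first. If it is so, the labels in the paragraph are wrong and still need correcting.
- **The size depends on an SD that the documents do not give.** This stands, and the result is therefore shown as a range. A correlation well above 0.7 would raise power further: at 0.9 the SD of change is 0.51 mm and power for 1.0 mm exceeds 99%. The protocol states no such correlation and does not use one.

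Two stronger readings are tempting but unsupported:

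- **That the protocol itself predicts no difference.** The Results section does say "Although a substantial difference between the groups is not anticipated". The same sentence goes on to expect better CAL gain and PPD reduction with AmnioGuard, and the sentence before it concerns plaque index. The passage is ambiguous and the point does not rely on it.
- **That the trial will probably miss a clinically relevant difference, or plans to claim equivalence.** The article sets no relevance threshold. At 1.0 mm, power exceeds one half for two of the three assumed correlations. Statistical Analysis calls P above .05 only not significant and announces no equivalence claim.

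**Conclusion.** The sample size justification is wrong as written. The 95% power was derived for a 1.7 mm within-arm change. It would carry over to the between-arm PPD comparison only if AmnioGuard beat an active comparator by about its own whole treatment effect. It does not apply to bone fill at all.

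Under the assumptions above (ρ from 0.3 to 0.7, the document's SDs in both arms, 12 per arm, no dropout), 80% power is reached for differences between 1.06 and 1.61 mm, and power for 1.0 mm lies between 41% and 76%. The mismatch of contrast is certain from the labels as printed. The size of the power shortfall is conditional on the assumed difference and correlation. None of this shows that 24 patients is the wrong number, because the article gives no between-arm target against which to judge it.

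**What to change.** 1. Check the 8.6 and 6.9 mm figures against the cited source. If they turn out to be values for two arms, correct the labels.
2. If they are one arm's before and after values, as labelled, withdraw the 95% power statement and keep n=24.
3. State instead what 12 per arm can detect, naming the assumption. Suggested wording: With 12 participants per group, a two-sided 5% t test and an assumed SD of PPD reduction of 1.14 mm (range 0.88 to 1.34 mm, for before-after correlations of 0.7 to 0.3), the trial has 80% power for a between-group difference of 1.36 mm (range 1.06 to 1.61 mm).
4. State that no power has been calculated for the primary outcome, radiographic bone fill, unless an SD for bone fill is supplied and the calculation is added.
5. Report between-group differences with 95% CIs, and do not read non-significance as equivalence.

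The cost is one source check and a rewritten paragraph. The stated power becomes less favourable. No extra patients are needed and no trial procedure changes. With 4 participants enrolled at submission, the correction can be made well before results are known.
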